Typical ICU-related therapy variables to collect daily include: ventilation variables, need for lung rescue therapy (such as prone ventilation, extracorporeal membrane oxygenation or oscillator), analgo-sedation variables (including sedations scores, using for example, the Richmond Agitation Sedation Scale (RASS) [24], and delirium scores, using for example, the Confusion Assessment Method (CAM-ICU) [25], pain score using, for example, a 10-point score, cumulative dose of sedatives and analgesics (including fentanyl, morphine, midazolam, and propofol), and fluid resuscitation variables including cumulative fluid balance [26], amount and type of infused fluids (for example, crystalloids, colloids and albumin), and daily amount of enteral/parenteral nutrition [27]. After the first 14 days, data on tracheotomies are collected.

Any surgical procedure, the amount of blood loss, presence of serious bleedings (defined as any clinically important bleeding from the lung (prompting bronchoscopy) or any clinically important bleeding requiring surgery or transfusion of clotting factors or blood products (red cells, platelets, plasma) is reported. Type and number of units transfused are specified as well as reasons to (temporarily) discontinue study medication, as described above, are reported as well.

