### Study endpoints

The primary endpoint - is the number of ventilator-free days, defined as the number of days alive and breathing without the assistance of a ventilator during the first 28 days. Thus, a patient must be free of ventilation for 24 hours to have one ventilator-free day. If, after successful extubation the patient requires re-intubation and ventilation due to a surgical procedure, this episode will not count as a ventilator day. However, if after surgery, ventilation is prolonged due to respiratory insufficiency, the day(s) will be counted as ventilator days.

Secondary endpoints - are subdivided into clinical and laboratory outcome variables and safety variables. Clinical outcome variables include: (a) length of stay (ICU and hospital); (b) mortality (28- and 90-day); (c) mortality (ICU and hospital); (d) daily LIS; (e) daily OI; (f) daily SOFA scores; (g) cumulative dosages of sedatives; (h) incidence of VAP; (i) total number of bronchoscopy-guided cleanings of the larger airway. Laboratory outcome variables include: (a) levels of markers of coagulation and fibrinolysis in blood and lung lavage fluid, including but not limited to tissue factor, activated factor VII, antithrombin, thrombin-antithrombin complexes, activated protein C, plasminogen activator activity, tissue plasminogen activator, urokinase plasminogen activator, plasminogen activator inhibitor 1, fibrin degradation products and plasma levels of heparin; (b) levels of markers of inflammation in blood and lung lavage fluid, including but not limited to IL-1beta, IL-6, IL-8, IL-10, TNF-alpha, growth factors and markers of complement activation; and (c) biological markers of lung injury in blood and lung lavage fluid, including but not restricted to total protein, albumin and IgM, Clara Cell 16 protein and soluble receptor for advanced glycation endproducts. Safety variables include (a) occurrence of relevant bleedings - requiring surgery, requiring transfusion of clotting factors, requiring transfusion of blood products (red cells or platelets or plasma), any clinically important bleeding from the lung (prompting bronchoscopy); (b) any other transfusion of blood products - red cells or platelets or plasma; (c) confirmed HIT; and (d) prolonged activated partial thromboplastin time (aPTT > 150 seconds).

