Interim analysis - blind interim analysis for safety is performed after 58 patients are successfully included and reached the endpoint. Suspected unexpected serious adverse events (SUSARs) and serious adverse events (SAEs) (any death; all serious bleedings requiring surgery, transfusion of clotting factors or blood products; any clinically important bleeding from the lung; requirement of transfusion of blood products; and confirmed heparin-induced thrombocytopenia) that are possibly related to study medication will be compared using the Chi-square test. If the data safety monitoring board (DSMB) (see below) has concern regarding the incidence of serious adverse events, it can request unblinded data. The investigators will remain blinded for the groups until the study is completed. If complications occur significantly more often in the intervention group (*P* ≤ 0.05), the study is terminated due to harm.

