### Statistical analysis

Patient characteristics will be compared and described by appropriate statistics. Data will be analyzed on an intention-to-treat basis. Normally distributed variables will be expressed by their mean and standard deviation and non-normally distributed variables will be expressed by their medians and 95% confidence levels. Categorical variables will be expressed as N (%). To test for normality, a D’Agostino and Pearson omnibus test will be performed [33]. Differences between groups will be tested by Student’s *t*-test for normally distributed data and Mann–Whitney *U*-test for not normally distributed data. Categorical variables will be compared with the Chi-square test or Fisher’s exact tests or when appropriate as relative risks. The difference of the primary effect variables will be analyzed using the Mann–Whitney *U*-test. The rate of freedom from ventilation will be analyzed according to the Kaplan-Meier method [34] and the results will be compared with the log-rank test hazard ratio’s are reported with 95% confidence limits. To take into account the stratification factors, we will perform an adjusted analysis. TBSA levels are group level data that will be included as a second level covariate in a multilevel linear regression model to assess the adjusted effect of our randomized treatment. Also the treatment effect on coagulation markers is investigated. Because they are clustered within each patient (repeated measurements) we will also use a multilevel model to evaluate the influence of the cluster effect on the model fit, that is we will compare the model fit without a second level (the patient) with the model fit that includes the patient as a second level. When appropriate, statistical uncertainty will be expressed by the 95% confidence levels. Statistical significance is considered to be at a *P* of 0.05. Analysis will be performed with SPSS version 18.1 (SPSS Inc., Chicago, IL, USA).

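### The interim harm comparison treats transfusion only as required or not, although units are recorded, so it could miss a rise in the amount transfused

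*Protocol article*

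**What the plan says.** **Interim look** (Statistical considerations, Interim analysis). A "blind interim analysis for safety is performed after 58 patients are successfully included and reached the endpoint". The list of events covers deaths, serious bleedings and lung bleeding, and ends: "requirement of transfusion of blood products; and confirmed heparin-induced thrombocytopenia) that are possibly related to study medication will be compared using the Chi-square test". The harm criterion is that "complications occur significantly more often in the intervention group", at P ≤ 0.05.

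**Data collected** (Follow-up). "Type and number of units transfused are specified". Daily data run to first ICU discharge or death, for at most 28 days.

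**Safety variables** (Study endpoints). Item (a) is relevant bleeding, including bleeding that needs transfusion. Item (b) is "any other transfusion of blood products - red cells or platelets or plasma". No scale is given for (b).

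**Test rules** (Statistical analysis). "Categorical variables will be compared with the Chi-square test or Fisher’s exact tests". Mann-Whitney is assigned to variables that are not normally distributed. No rule is specific to transfusion.

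**The concern.** A transfusion requirement takes two values. A patient given two units and a patient given twenty count the same. If many patients in both arms receive at least one unit, for example around surgery, the proportion transfused has little room to rise, and a treatment that mainly increases the amount of blood product per patient leaves it almost unchanged.

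The Discussion names serious bleeding as a major safety concern and says that safety data in this population are limited. The interim Chi-square is the formal comparison tied to the harm criterion. A non-significant result on the requirement could be read as no excess need for blood products, while the unit counts that might show otherwise sit unused in the case report form.

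**Working it through.** **Inputs from the protocol article.** Final size is 58 per arm. That figure reproduces from the primary endpoint: pooled SD = √((4.0² + 7.1²)/2) = 5.76, difference 3 days, two-sided 0.05 and 80% power give 2 × (1.960 + 0.842)² × 5.76²/3² ≈ 58. It says nothing about transfusion; it only sets the group sizes. The interim has 58 patients, so 58/2 = 29 per arm under equal allocation. The harm threshold is P ≤ 0.05, taken as two-sided.

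**Inputs that must be assumed.** The documents give no transfusion rate, no mean number of units and no spread. Units per patient are taken as negative binomial with mean m and shape k.

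**Step 1: how far the yes/no rate can move.** With control rate p0:
- m = k × ((1 − p0)^(−1/k) − 1)
- if heparin multiplies the mean by r, the treated rate is p1 = 1 − (k/(k + r·m))^k

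Example with p0 = 0.90 and k = 1: m = 1/0.10 − 1 = 9. Doubling gives a mean of 18 and p1 = 1 − 1/19 = 0.95. Twice the blood product moves the yes/no rate by five points.

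**Step 2: Chi-square power for that shift.** Power = Φ[(Δ√n − 1.96√(2p̄(1 − p̄)))/√(p0(1 − p0) + p1(1 − p1))].
- n = 29, 0.90 v 0.95: (0.05 × 5.385 − 1.96 × 0.3725)/0.3708 = −1.24, so 0.107 (exact enumeration 0.098)
- n = 58: (0.05 × 7.616 − 0.730)/0.3708 = −0.94, so 0.173 (exact 0.167)

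**Step 3: both tests on the same simulated data.** Mean units doubled, k = 1, 2,000 runs per cell, significant results in the harm direction:

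| Any transfusion, control → heparin | Interim Chi-square | Interim Mann-Whitney on units | Final Chi-square | Final Mann-Whitney on units |
|---|---|---|---|---|
| 30% → 46% | 25% | 31% | 43% | 52% |
| 50% → 67% | 24% | 40% | 42% | 69% |
| 70% → 82% | 20% | 50% | 34% | 80% |
| 80% → 89% | 15% | 54% | 28% | 84% |
| 90% → 95% | 9% | 57% | 14% | 86% |

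**Step 4: sensitivity to the assumptions.**
- Another set of assumed means and shapes, with control rates of 21% to 91%, gives for a doubling about 8-17% (Chi-square) v 19-57% (Mann-Whitney) at 29 per arm, and 16-29% v 32-86% at 58.
- Over k = 0.7 to 2 and control rates of 30% to 90%, a doubling gives 7-34% v 24-81% at 29 per arm.
- At a 30% control rate alone, over the same shapes, it is 18-28% v 24-33% at 29 per arm and 36-51% v 46-62% at 58.
- For a 1.5-fold rise at 29 per arm, it is 5-14% v 12-38%.
- If the harm is one extra bleed of 2-4 units in 10% to 20% of patients, with 55% to 91% of controls transfused, the gain at 58 per arm is 0 to 10 points.

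The test on units was essentially never the weaker one. How much it gains depends on the control rate and on the form of the harm.

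**The case against.** A reader might infer that transfusion is known to be common here, that the final comparison is also yes/no, and hence that the whole trial has little chance of seeing a transfusion harm. The documents do not support that.

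- **Base rate.** Nothing in the article says that transfusion is common. Patients without skin burns are eligible and burns above 60% of body surface are excluded. A high rate is plausible, since surgery under general anesthesia is foreseen, but it is an assumption.
- **Relatedness.** The interim rule counts only events possibly related to study medication. Transfusions put down to surgery or the burn may be left out, so the counted rate may be well below its ceiling. The simulation counts every transfusion.
- **Final analysis.** In safety variable (b), the opening words set these transfusions apart from those in (a); they do not fix a yes/no scale. The general rules already allow Mann-Whitney on units, and an analysis plan that is not shown may name the scale.
- **Power is not always low.** A yes/no test at 58 per arm has about 60-66% power for a 20-point rise from 50-60%. At 29 per arm it has 34-38%.
- **Sample size.** Mann-Whitney on units also stays weak at the interim for a 1.5-fold rise, so part of the weakness comes from having 29 per arm.
- **Other safeguards.** Serious and lung bleeding are separate items, and the DSMB receives serious events within 24 hours and can ask for unblinded data.

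All of this stands, and it limits the point to the interim comparison and to a conditional loss. It does not remove the point. The interim form is stated explicitly and the counts are in hand. Access to unblinded data depends on the DSMB already being concerned, which a blunt variable is less likely to bring about.

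**Conclusion.** The point holds for the interim harm comparison: transfusion enters as a requirement, filtered by judged relatedness, although units are recorded. If many patients in both arms are transfused, this would largely miss an increase in amount. For a doubling at 29 per arm, power is about 8-17% against 19-57% for units, over assumed control rates of 21-91%. The result rests on assumed negative binomial counts and on a treatment effect that multiplies units across patients. The gain is small if few patients are transfused or if the harm is a handful of extra bleeds.

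For the final analysis, the documents show only that the scale of safety variable (b) is open, not that it is yes/no. This is an inexpensive improvement to safety monitoring, not evidence that the trial cannot detect bleeding harm.

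**What to change.** **Interim analysis.** Keep the Chi-square comparison. Add for the DSMB, by coded arm, the units transfused per patient, separately for red cells, platelets and plasma. Include all transfusions whatever their judged relatedness, and compare by the Mann-Whitney test that the plan already uses.

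**Study endpoints and Statistical analysis.** State that transfusion is analysed as units per patient on the same scale, with the percentage receiving any transfusion shown beside it.

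**Period.** Count units over the time in which they are collected: to first ICU discharge, death or day 28, whichever comes first. A total for every patient to day 28 would need data that the Follow-up section does not describe. Also show units per day under collection, since its length may differ by arm. A rate per day alive would not do, because patients discharged from ICU are alive but no longer under daily collection.

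**Cost.** A few sentences and one extra table, with no new data. The drawback is that total units depend on ICU stay and survival; the per-day display makes that visible but does not remove it.

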### Study organization

The Steering Committee is composed of the principal investigators of the participating centers who contribute to the design and revisions of the study protocol. The national coordinators in the Netherlands and in Belgium ensure that all local necessary ethical and regulatory approvals are obtained before start of patient inclusion. In individual participating centers, local coordinators provide scientific and structural leadership in their center. They guarantee the integrity of data collection and ensure timely completion of case report forms (CRFs). The trial coordinator trains and monitors the participating centers to ensure the study is conducted according to ICH-GCP guidelines [35], guarantees the integrity of data collection and ensures timely completion of CRFs. An independent monitor performs study monitoring. The independent DSMB is composed of four independent persons ([name]. [name], [name]. [name], [name]. [name], and [name]. [name]). The DSMB reviews the overall status of the program (number of patients enrolled overall and in each center, adherence to the protocol overall and by each center) and receives an interim analysis on safety (described below). The DSMB will meet by conference calls. The first meeting is scheduled after 15 patients are enrolled. Subsequent to this meeting, the DSMB will meet every six months.

All adverse events reported are sent to the DSMB for review in a blinded fashion. All (possibly) related and unrelated severe adverse events (SAEs) and suspected unexpected serious adverse reactions (SUSARs) will be sent to the DSMB within 24 hours after being received by the coordinating center. Non-serious study-related adverse events will be sent every week. Non-serious study-unrelated adverse events are recorded in an overview list (line-listing), submitted once every half year.

If the DSMB has concern regarding the incidence of SAEs, the DSMB can request and will be supplied with unblinded data. The investigators will never see these data. When complications occur significantly more often in the intervention group (*P* ≤ 0.05), terminating the study due to harm will be considered.

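### As written, the only planned interim between-arm safety test covers just the events judged possibly related to study drug, so an excess of deaths or bleeds put down to the burn or surgery would not be tested

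*Protocol article*

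**What the plan says.** Under Statistical considerations (Interim analysis), the protocol article states that a "blind interim analysis for safety is performed after 58 patients are successfully included and reached the endpoint". The serious adverse events of interest are listed in parentheses and open with "any death; all serious bleedings requiring surgery, transfusion of clotting factors or blood products; any clinically important bleeding from the lung"; transfusion requirement and confirmed heparin-induced thrombocytopenia (HIT) follow. The sentence then narrows what is compared to events "that are possibly related to study medication will be compared using the Chi-square test". The same paragraph says that if complications are significantly more frequent in the intervention group, at P of 0.05 or less, "the study is terminated due to harm".

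Study organization describes what reaches the DSMB: "All (possibly) related and unrelated severe adverse events (SAEs) and suspected unexpected serious adverse reactions (SUSARs) will be sent to the DSMB within 24 hours", and "All adverse events reported are sent to the DSMB for review in a blinded fashion". The DSMB may ask for unblinded data if SAE incidence concerns it. This section repeats the harm criterion, again for complications without a relatedness condition, but here "terminating the study due to harm will be considered". The Discussion also says the trial stops on a significant excess of complications in one arm, again without that condition.

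Mortality and bleeding appear without a relatedness filter under Study endpoints, as secondary and safety variables. No interim test is attached to them there.

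**The concern.** Randomisation with blinding makes a comparison of all events by arm a valid test of harm, with no need to judge individual cases. A relatedness filter replaces part of that comparison with case-by-case opinion. The setting makes such opinion hard: the Background says about one third of burn patients with inhalation trauma die, and surgery is expected during the stay. A death or bleed that heparin caused or worsened may have a ready alternative explanation and drop out of the test.

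The Discussion names serious bleeding as a major concern and calls the safety data in this population limited. The interim analysis is the only planned comparison by arm before the second 58 patients complete the trial. The unfiltered mortality and bleeding endpoints come too late to protect them.

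**Working it through.** **Which events does the harm comparison cover?**

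- Interim analysis, event list: every death and every serious bleeding, without qualification.
- Interim analysis, comparison: only those possibly related to study medication.
- Interim analysis, Study organization and Discussion, harm criterion: complications, with no relatedness condition.

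The test is filtered; the list and the stopping wording are not.

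**Inputs.** The protocol states no event rate, attribution share or power for the interim test, so there is no figure of its own to reproduce.

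- Interim size: 58 patients, so 58/2 = 29 per arm (equal allocation assumed from the planned 58 + 58).
- Test: Pearson chi-square, P ≤ 0.05, as stated. Assumed: no continuity correction, patients counted once, excess in the heparin arm.
- Assumed for illustration: true mortality of 45% on heparin and 20% on placebo, and the shares of deaths judged related.

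**Formula.** With a and b events in n = 29 per arm and p = (a + b)/58, z = [(a − b)/29] / √[p(1 − p) × 2/29]. The chance of a flag is the sum of the binomial probabilities of all (a, b) with a > b and two-sided P ≤ 0.05, by exact enumeration.

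**One observed split.**

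- 18 v 10 deaths: p = 28/58 = 0.483, z = 0.276/0.131 = 2.10, P = 0.036. The criterion is met.
- Half of each judged related, 9 v 5: p = 14/58 = 0.241, z = 0.138/0.112 = 1.23, P = 0.22. It is not met.

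**Same share judged related in both arms.**

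| Deaths counted | Heparin | Placebo | Chance of a flag |
|---|---|---|---|
| All | 45% | 20% | 53% |
| Half | 22.5% | 10% | 25% |
| A quarter | 11.25% | 5% | 13% |

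Starting from the one-third mortality in the Background and an assumed rise to 60%, the chances are 53% (all), 22% (half) and 13% (a quarter). For assumed bleeding rates of 30% v 10% they are 48%, 25% and 9%.

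**Different shares for background and excess deaths.** Again 45% v 20%: background deaths are 20% in each arm and the excess is 25% in the heparin arm. The counted rate is 0.20 × s on placebo and 0.20 × s + 0.25 × e on heparin, where s and e are the shares of background and excess deaths judged related.

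| s | e | Heparin | Placebo | Chance of a flag |
|---|---|---|---|---|
| 25% | 50% | 17.5% | 5% | 35% |
| 50% | 75% | 28.75% | 10% | 44% |
| 25% | 75% | 23.75% | 5% | 58% |
| 10% | 75% | 20.75% | 2% | 70% |

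Against 53% unfiltered, the filter loses in the first two rows and gains in the last two.

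**Blinded counts.** 45% v 20% pools to (45 + 20)/2 = 32.5%, close to the one third in the Background, so pooled mortality would raise no alarm. One third v 60% pools to about 47%, which might.

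**The case against.** The strongest reply is that the sentence may not mean what it literally says. Words covering every death and every serious bleeding sit badly with filtering case by case, and the relatedness clause could describe event types heparin might plausibly cause. The article describes no attribution step and does not say who would judge. That stands as an ambiguity, not as a defence: the plain grammar filters the events, and someone following it literally would leave unrelated deaths out.

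Second, the DSMB sees unrelated events within 24 hours, meets after 15 patients and then every six months, and can obtain unblinded data. A reader might infer that an excess of unrelated events would stay hidden. The documents do not support that; some excesses would show even in pooled counts. But the route depends on concern arising from blinded review, and it is not a planned test.

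Third, a reader might infer that the filter always reduces power. That is not established. The listed harms include recognised heparin effects, and possible relatedness is a low threshold, so drug-caused events may be recognised more often than background ones. The last two rows of the second table show the filtered test doing better.

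Finally, this is a condensed article, and the full protocol or a DSMB charter may define causality assessment. That could explain how the filter is applied; it would not remove the filter from the rule stated here.

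**Conclusion.** The point holds in this form: on its plain reading, the only planned interim comparison by arm excludes events not judged possibly related, and this does not match the unqualified event list or the three statements of the harm criterion. Deaths or bleeds attributed to the burn or surgery would go untested at the interim, with discretionary DSMB unblinding as the only backstop.

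The size is conditional. With 29 per arm and 45% v 20% mortality, the chance of a flag falls from 53% to 25% or 13% if attribution is equally incomplete in both arms. It is 35% to 44% with moderately better recognition of excess deaths, and 58% to 70% with much better recognition. Mortality rates and attribution shares are assumptions throughout. What is firm is that the test's ability to detect harm rests on an unstated attribution process, when a comparison free of that dependence is available from data already collected.

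**What to change.** Remove the relatedness restriction from the interim analysis sentence. Compare by coded arm, regardless of attribution, all deaths, all serious bleedings (including from the lung) and confirmed HIT. Show each event type separately and report the possibly related subset as a supplement, so nothing in the present plan is lost.

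Do not pool transfusion with the rest. If, for illustration, 60% to 80% of patients had a background event and harm affected a quarter of the others (60% to 70%, or 80% to 85%), a pooled comparison would flag it only 11% to 7% of the time.

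Reconcile the Interim analysis paragraph, Study organization and the Discussion on which events the harm comparison covers. They also differ on whether termination follows or is considered, and on whether the excess must be in the intervention arm or in either arm; these too must be reconciled.

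The cost is a few sentences. No new data are needed, because related and unrelated SAEs already go to the DSMB, and investigators stay blinded. The downside is somewhat noisier counts from background events. Several separate comparisons also mean more than one chance of a false flag, so the text should say which of them the 0.05 criterion applies to.
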